#### Follow-up

Three months after the post-treatment assessment a follow-up session will be conducted. This session will repeat baseline and post-treatment assessments, except that no MRI scan will be conducted. A qualitative semi-structured interview will also be undertaken with participants (minimum of n = 10 from each real/sham group) to ascertain their views on and experience of this treatment. Finally, blinding success will be evaluated by asking participants and researchers to guess the treatment allocation. Participants will be unblinded and individuals in the sham rTMS group will then be offered the real rTMS treatment.

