**Design:**

Forty-four adults from the community with a DSM-5 diagnosis of AN, an illness duration >3 years and a previous course of unsuccessful treatment will be randomly allocated to receive 20 sessions of either real or sham rTMS, in a parallel group design. As this is a feasibility study, no primary outcome has been defined and a broad range of outcome variables will be examined. These include weight/body mass index (BMI), eating disorder psychopathology, other psychopathology (for example, depression, anxiety), quality of life, neuropsychological processes (such as self-regulation, attentional bias and food choice behaviour), neuroimaging measures (that is, changes in brain structure or function), tolerability and acceptability of rTMS, and additional service utilisation.

The feasibility of conducting a large-scale RCT of rTMS and the appropriateness of rTMS as a treatment for SEED-AN will be evaluated through: assessment of recruitment and retention rates, acceptability of random allocation, blinding success (allocation concealment), completion of treatment sessions and research assessments (baseline, post-treatment and follow-up assessments). The acceptability and tolerability of the treatment will be assessed via semi-structured interviews.

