##### Intervention/service related outcomes

Treatment expectations, tolerability and acceptability of rTMS will be assessed by VAS and thematic analysis of semi-structured interviews.Service utilisation of treatments and services other than rTMS will be assessed with a self-report version of the Clinical Service Receipt Inventory (CSRI) [97].

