### Analyses

#### Feasibility

The decision as to whether to progress the study to a future large-scale RCT will be based on a number of criteria. These include the number of patients we are able to recruit, the proportion of patients retained in the study, the proportion of patients completing the real rTMS/sham intervention, the acceptability of real rTMS/sham intervention and the effect sizes of treatment outcomes. At the end of the study, these factors will be used by the study team to decide the case for progressing to a substantive RCT.

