#### Qualitative data

Interviews will be conducted with a minimum of ten participants from each of the groups, recruited according to key characteristics (such as previous treatment history), until theoretical saturation is reached. Interviews will explore initial expectations of the intervention, perceived strengths and weaknesses, and suggestions for improvements. Interviews will be recorded, transcribed and analysed using thematic analysis [102].

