## Discussion

Treatment outcomes for psychotherapies are modest for adults with AN, and there is currently no gold-standard treatment [103]. Given the paucity of effective treatments for adult AN, specifically SEED-AN, new treatments are needed. In light of this, and with the growing understanding of the neural underpinnings of AN, research into novel non-invasive brain-directed therapeutic approaches is warranted [28, 45, 46]. This paper has outlined the protocol for a feasibility trial that will inform future studies (for example, provide effect sizes for a large RCT) and add to the evidence for brain-directed interventions for AN [57, 58, 104], [name] et al., unpublished observations. Strengths of the study include the use of an individualised (neuronavigated) neuromodulation technique. Moreover, the protocol is designed to probe disease mechanisms (that is, with the inclusion of multiple structural and functional neuroimaging measures) and will provide important insight into the neural correlates of the therapeutic effect. Finally, the protocol adheres to guidance on the optimal conduct of neuromodulation trials [105–107].

Several potential practical and operational issues may pose challenges to the timely completion of this study, particularly with regards to recruitment and attrition. Patients with AN are often ambivalent about treatment and this is reflected in poor take-up rates of certain treatments (for example, medications leading to weight gain) and high drop-out rates [108]. Whilst rTMS appears promising in AN, it is unclear what the take-up, attendance, and retention rates will be if this is offered to SEED-AN patients. Although participants who took part in our previous single-session rTMS trials [[name] et al., unpublished observations] showed interest in having rTMS therapeutically, adherence and completion of the treatment may prove challenging, for example, if the participant believes they are receiving sham, if the treatment is too uncomfortable or if the research is too cumbersome.

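### The acceptability interview sits in the 3-month follow-up session, so people who leave the study earlier are not reached and early stoppers need not be sampled; the interview evidence may be too favourable.

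*Protocol article*

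**What the plan says.** **Timing.** The Follow-up section sets the visit: "Three months after the post-treatment assessment a follow-up session will be conducted". Within that session it adds: "A qualitative semi-structured interview will also be undertaken with participants (minimum of n = 10 from each real/sham group"). Blinding is lifted at the end of the same visit.

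**Sampling.** The Qualitative data section says that interviewees are "recruited according to key characteristics (such as previous treatment history), until theoretical saturation is reached". Previous treatment history is the only characteristic given, as an example. Neither section mentions an interview at exit or sampling by whether the rTMS course was completed.

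**Role of the interview.** The abstract (Design) says: "The acceptability and tolerability of the treatment will be assessed via semi-structured interviews". The section on intervention and service related outcomes names a second instrument: "Treatment expectations, tolerability and acceptability of rTMS will be assessed by VAS and thematic analysis of semi-structured interviews".

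**Use.** The Feasibility section under Analyses includes among the progression criteria "the acceptability of real rTMS/sham intervention and the effect sizes of treatment outcomes". It lists separately "the proportion of patients retained in the study, the proportion of patients completing the real rTMS/sham intervention".

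**Expected difficulty.** The Discussion warns that "adherence and completion of the treatment may prove challenging". Its examples are a belief that one is receiving sham, discomfort from the treatment, and the burden of the research.

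**The concern.** The Discussion allows that people may not complete for reasons that bear on acceptability. The interview is then held after that loss has happened, about four months after the first session. The people best placed to explain why rTMS, or the trial around it, was not tolerable are the least likely to be in the room.

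There may be a further pull in the same direction. Real rTMS is offered to the sham group after follow-up, and the Discussion regards this offer as important for retention. Those who attend may therefore lean towards people who want rTMS.

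Two things are at stake. Acceptability feeds the decision on a large trial, so a one-sided account would favour progression. The interviews are also meant to gather weaknesses and suggested improvements, and the causes of drop-out that a later protocol could correct are what leavers would describe. Their accounts cannot easily be recovered once they have disengaged.

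**Working it through.** **1. The plan's own figure.** The Sample size section takes a target of 40 and attrition to follow-up of a = 0.10, and inflates by 1/(1 − a):

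40 / (1 − 0.10) = 44.4

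The plan states 44 (22 per group). The figure reproduces, apart from rounding down instead of up.

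**2. When the interview happens.** Twenty consecutive weekdays make four weeks of treatment. The post-treatment assessment falls in the week after, and follow-up is three months after that. The interview therefore comes roughly four months after the first session.

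**3. Who can be interviewed.**

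| Group | Reached by the interview as planned? |
|---|---|
| Completes rTMS, attends follow-up | Yes |
| Stops rTMS early, stays in the study | Can be, but not required by the sampling rule |
| Leaves the study before follow-up | No |

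The second row rests on the safety section, which says that patients with mild side effects are not withdrawn and may stop rTMS if they wish.

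**4. How many are not reached.** At the planned attrition, 44 × 0.10 = 4.4, about 4 people. The Discussion calls retention for this treatment unclear, so 20% (44 × 0.20 = 8.8, about 9) and 30% (44 × 0.30 = 13.2, about 13) are shown as assumptions.

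**5. What this could do to a proportion.** The article gives no acceptability rates and derives no percentage from the interviews, so this step is only a scale for the concern. Let p be the share of those seen who find rTMS acceptable and q the share among leavers.

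overstatement = p − (n_seen × p + n_lost × q) / 44 = (n_lost / 44) × (p − q)

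With p = 80% assumed:

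| Attrition | Lost | q = 0% | q = 20% | q = 50% | q = 80% |
|---|---|---|---|---|---|
| 10% | 4 | 7.3 points | 5.5 | 2.7 | 0 |
| 20% | 9 | 16.4 | 12.3 | 6.1 | 0 |
| 30% | 13 | 23.6 | 17.7 | 8.9 | 0 |

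At 10% attrition the ceiling for any p and q is 4/44 = 9.1 points.

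**6. Room within the planned interviews.** The minimum is 10 per arm, 20 in total. If leavers were eligible and 20 of 44 were drawn at random, 20 × 4/44 = 1.8 of the 4 leavers would be included on average, and none would be included with probability C(40,20)/C(44,20) = 7.8%. Sampling is purposive, so this is only a benchmark. Under the stated timing the number of leavers interviewed is zero by construction.

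**The case against.** The strongest reply has five parts.

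- **Stopping rTMS is not leaving the trial.** A reader might infer that everyone who stopped rTMS is missed. The article does not support that. Patients who stop because of mild side effects are not withdrawn, the analysis follows intention to treat, and the interview is open to participants, not only to completers. This stands. For early stoppers the point is only that nothing ensures that any are chosen.
- **Other sources exist.** Acceptability is also rated by VAS. Numbers and reasons for withdrawal are recorded (Screening section), attendance and side effects go on a case record form, and retention and completion count towards progression in their own right. This stands in part. Drop-out is not ignored, but a count and a recorded reason do not replace an account of expectations, weaknesses and improvements. The article does not say when the acceptability VAS is taken, and the within-session VAS items that it lists concern symptoms and urges.
- **Upward bias is not shown.** A reader might infer that acceptability will be overstated by a calculable amount. The interviews are analysed by theme, with no percentage or threshold, and leavers' views are unknown. Two of the Discussion's three examples, believing one is on sham and research burden, are not objections to rTMS itself, and the passage is conditional. This stands: direction is plausible, size is not derivable.
- **An article condenses.** The full protocol and Additional file 1 are not shown and may provide for exit interviews, and treatment history is only an example. The possibility is real. But the article does not merely leave the timing out: it places the interview in the 3-month session, and that stated timing excludes leavers.
- **Four leavers make a poor comparison group.** Some will decline, and interviews at exit and at three months are less comparable. This stands and shapes the fix.

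**Conclusion.** The point holds in a limited form. Followed as written, the plan does not interview people who leave before the 3-month session, and it does not require that people who stop rTMS early but remain be among those interviewed. The interview evidence on acceptability may therefore be too favourable and may lack reasons for leaving. The other sources named in the plan narrow the gap without closing it.

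The affected number is about 4 of 44 if the planned 10% attrition is met, and more if it is not. The table in the working rests on an assumed 80% acceptability among those seen and on assumed views among leavers. It includes zero at every attrition rate. It should not be cited as an estimate of bias, because the plan estimates no such proportion. The main loss is of themes. The conclusion also assumes that the full protocol repeats the timing given in the article.

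**What to change.** In the Follow-up section, add that any participant who discontinues rTMS or withdraws is offered the same interview at that time, by telephone if preferred and before unblinding, if they agree. Those who complete and stay keep the 3-month timing.

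In the Qualitative data section, name completion of the rTMS sessions as a sampling characteristic beside treatment history. Identify the themes raised by non-completers descriptively, and state how many were approached and how many declined. A formal comparison of completers with non-completers is not worth planning with so few people.

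The cost is a minor amendment and, at the planned attrition, about four interviews by the existing team, which can count towards the minimum of 10 per arm. There are two small downsides: some people who withdraw will decline, and interview timing will differ between leavers and stayers, which the report should state. If the full protocol already provides for this, a sentence in the article is enough.

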### Measures

#### Screening measures

BMI (kg/m^2^)Screening questionnaires:Eating Disorder Diagnostic Scale (EDDS) [72]: This will be used to confirm ED diagnosis. A revised version of the original EDDS incorporating the diagnostic changes in the DSM-5 will be used, although this has not yet been validated [73].Screening module of the Structured Clinical Interview for DSM Disorders – Researcher Version (SCID) [74]: This short semi-structured psychiatric interview will be used as a diagnostic screen to assess the presence of psychiatric comorbidities.MRI Safety Screen: This was created at the Centre for Neuroimaging Sciences at King’s College London and will be used to ensure the participant is safe to undergo an MRI scan.TMS Adult Safety Screen [75]: This will be conducted to check for contraindications to rTMS.Other safety assessments: physical observations: blood pressure (sitting and standing), pulse, and routine blood tests.

#### Within-session measures

In all rTMS sessions, participants will complete several VASs before and after rTMS. These will assess perceived levels of stress, anxiety, feeling full, feeling fat, urge to restrict, urge to exercise, urge to binge, urge to purge and mood. At the end of each week, ED and mood symptomatology will be assessed using three short questionnaires: the Eating Disorder Examination Questionnaire short version (EDE-QS) [76], the Fear of Food Measure (FoFM) [77] and the 21 item Depression, Anxiety and Stress Scales (DASS-21) [78].

#### Outcome measures

Since this is a feasibility study, a broad range of outcome measures are included to help determine which are most sensitive to detecting a treatment effect. This will enable us to determine primary outcome(s) for a future large-scale RCT. However, the Eating Disorder Examination Questionnaire (EDE-Q) and DASS-21 scores are the most likely candidates (based on our pilot data) [58].

#### Clinical outcomes

ED-related measures: BMI and ED symptomatology (measured by the EDE-Q version 6.0 [79], FoFM, and the Self-Starvation Scale (SS) [80] will be completed at baseline, post-treatment and at 3-month follow-up. Within each session, VAS regarding current ED experiences (urge to restrict, urge to binge, urge to purge, urge to exercise, feeling full, feeling fat, urge to eat, feeling low, level of stress, level of anxiety, level of tension, and current hunger) will be completed pre- and post-real/sham rTMS. The FoFM and the EDE-QS will additionally be completed weekly during treatment.Other symptomatology will be measured by questionnaires including the DASS-21, Positive and Negative Affect Schedule (PANAS) [81], Profile of Mood States (POMS) [82] and Intolerance of Uncertainty Scale (IUS) [83] at baseline, post-treatment and 3-month follow-up. The DASS-21 will additionally be completed weekly during treatment.Offline neuropsychological tasks assessing: i) inhibitory control as assessed by a proactive inhibition task [84] will be completed at baseline, post-treatment and 3-month follow-up, while ii) attentional bias to food using the visual probe task (VPT) [85, 86] and iii) food choice behaviour tasks (FCT) [87] will be conducted at baseline and post-treatment.Questionnaires assessing: i) impulsivity/compulsivity and self-regulation, that is, Delaying Gratification Inventory (DGI) [88], Barratt Impulsiveness Scale (BIS-11) [89] and Obsessive-Compulsive Inventory (OCI-R) [90], and ii) cognitive control of emotions and self-efficacy, including the Eating Disorder Recovery Self-Efficacy Questionnaire (EDRSQ) [91], Emotion Regulation Questionnaire (ERQ) [92] and the Cognitive Flexibility Scale (CFS) [93] assessed at baseline, post-treatment and 3-month follow-up, and iii) quality of life (EuroQol Quality of Life Scale EQ-5D-5 L [94]) and illness impact (Clinical Impairment Assessment (CIA)) [95, 96] will be assessed at baseline and 3-month follow-up.

##### Intervention/service related outcomes

Treatment expectations, tolerability and acceptability of rTMS will be assessed by VAS and thematic analysis of semi-structured interviews.Service utilisation of treatments and services other than rTMS will be assessed with a self-report version of the Clinical Service Receipt Inventory (CSRI) [97].

##### Neuroimaging outcomes

Magnetic resonance imaging (MRI) measures at baseline and post-treatment include:Structural MRI for neuronavigation of the rTMS coil and for assessing whole-brain structural changes after rTMS using T1 weighted images acquired through a magnetisation-prepared 180 degree radio-frequency pulse and rapid gradient-echo (MPRAGE) sequence (voxel size: 1.1 × 1.1 × 1.2 mm, TR: 7.312 ms, TE: 3.016 ms, number of slices: 196, slice thickness: 1.2 mm, slice gap: 1.2 mm, FOV: 11, flip angle: 11°, matrix: 256 × 256 mm);fMRI involving paradigms assessing inhibitory motor control in a Stop Signal Task (SST) [98] and motivation control, that is, temporal foresight and reward-related decision making in a temporal discounting (TD) task [99, 100]), using an echo planar imaging (EPI) sequence for both tasks (TR: 2,000 ms, TE: 30 ms, number of slices: 40, slice thickness: 3 mm, slice gap: 3.3 mm, number of volumes: SSRT = 193, TD = 363, FOV: 240, flip angle: 75°, matrix: 64 × 64 mm);Resting state fMRI to study neural networks at rest (TR: 2,500 ms, TE: 28 ms, number of slices: 32, slice thickness: 3 mm, slice gap: 4 mm, FOV: 240, flip angle: 80°, matrix: 64 × 64 mm);ASL to obtain a quantitative measure of cerebral blood flow at rest (TR: 5,135 ms, TE: 11.088 ms, number of slices: 56, slice thickness: 3 mm, slice gap: 3 mm, FOV: 240, flip angle: 111°, matrix: 512 × 8 mm).

#### Blinding

Participants and the researchers conducting assessments and delivering the rTMS will be blinded to treatment allocation throughout; that is, the study will be conducted in a triple-blind fashion. To assess whether allocation concealment has been successful, participants and the researcher will be asked to guess the treatment allocation at the end of the rTMS treatment and to indicate how certain they are of this guess. Participants (but not rTMS therapists in order for them to remain blinded throughout the study) will be debriefed and unblinded to group allocation upon completion of the 3 month follow-up. At that point participants in the sham condition will be offered real rTMS treatment following the same protocol as described above.

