#### Sample size

As this is a feasibility study, no a priori sample calculation has been conducted. This study aims to provide effect sizes on which future large-scale studies can be powered. Total sample sizes of *N* = 24–50 have been recommended for feasibility trials with outcomes measured on a continuous scale, mainly because estimates of the standard deviation for normally distributed variables tend to stabilise around this size [65, 66]. We have chosen a sample size of *N* = 40 (that is, at the upper end recommended for feasibility trials). Assuming the attrition to follow-up rate is a = 0.10 (as found in our previous AN trials [15, 67], [name] et al., unpublished observations and applying an attrition correction factor of 1/(1-a), we will need a total sample size of *N* = 44 (22 participants per group).

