Although we are using the most up-to-date equipment with an improved sham coil that elicits a more realistic TMS-like sensation, it is not clear whether participants, especially those who may have previous experience of rTMS in other research studies, will be able to distinguish between the real and sham treatment and what impact this will have on attrition rates. However, in our previous RCT of a single rTMS session in people with AN there was no difference between groups in the ability to correctly guess stimulation type [[name] et al., unpublished observations].

It will be important to ascertain patients’ willingness to undergo random allocation to real or sham rTMS. This is not trivial, as rTMS is a relatively demanding treatment, requiring daily attendance for an extended period. However, this type of RCT is considered the gold-standard method of evaluating the clinical efficacy of rTMS treatment in other disorders, such as depression [50]. Providing participants who were randomised to receive sham rTMS with the opportunity to receive real rTMS after they have completed the study is thought to be critical in encouraging recruitment and participant retention. Addressing these challenges will be particularly useful in informing the development of future large-scale RCT of rTMS in EDs.

In summary, research into novel treatments for SEED-AN is essential. rTMS is a promising neuromodulatory technique that has shown preliminary benefit in AN, including individuals with SEED-AN. This innovative feasibility RCT will be the first to systematically assess the acceptability, efficacy and neural correlates of this promising treatment in comparison to an active control condition. This will provide a foundation for the development of future large-scale RCTs and, if the results are positive, will provide support for the implementation of this as a treatment adjunct in clinical practice.

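### The allocation guess is planned only at the end of rTMS and at the 3-month follow-up, so patients who leave the study during the 20 sessions have no planned guess

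*Protocol article*

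**What the plan says.** The abstract's Design paragraph lists the feasibility measures as "assessment of recruitment and retention rates, acceptability of random allocation, blinding success (allocation concealment), completion of treatment sessions", among others, so blinding success is a declared result of the trial.

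The guess is placed at two times:

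- **Blinding section:** "participants and the researcher will be asked to guess the treatment allocation at the end of the rTMS treatment", together with a rating of how certain the guess is.
- **Follow-up section:** at the 3-month session, "blinding success will be evaluated by asking participants and researchers to guess the treatment allocation". Participants "will be debriefed and unblinded to group allocation upon completion of the 3 month follow-up" (Blinding section), so a guess at that session comes before unblinding.

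The article states no guess during the course of sessions and none at the moment a patient stops or withdraws.

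Two remarks in the Discussion bear on this. Adherence and completion may suffer "if the participant believes they are receiving sham". The authors also say it is unclear whether participants will tell real from sham and "what impact this will have on attrition rates".

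The Sample size section gives the only planned loss: "Assuming the attrition to follow-up rate is a = 0.10". The Screening section says that numbers of withdrawals and the reasons for them are recorded.

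**The concern.** A patient who leaves the study part-way through the 20 sessions reaches neither stated time. Choosing one of the two times, or using both, does not change that.

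The gap need not be random. The protocol itself names belief in being on sham as a possible cause of non-completion, so the patients without a guess may differ in belief from those who have one. Two things are at stake:

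- The blinding result describes the patients who reached the end of treatment and may not describe all who were randomised.
- For patients who leave during treatment, the link between perceived allocation and attrition raised in the Discussion cannot be described from the planned guesses.

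**Working it through.** **Inputs.** From the Sample size section: target 40, attrition to follow-up 0.10, 44 randomised, 22 per group. The numbers of correct guesses, and attrition of 20% and 30%, are assumptions made here for illustration.

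**The plan's own figure.** 40 / (1 − 0.10) = 44.4, which the plan gives as 44. Expected loss is 44 × 0.10 = 4.4, so about 4 patients, leaving 40.

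**Bounds on the pooled share of correct guesses.** Let half of those who stay guess correctly, and let the missing guesses be all wrong or all correct. The share among all 44 then lies between (0.5 × stayers) / 44 and (0.5 × stayers + lost) / 44.

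| Attrition | Lost | Stay | All missing wrong | All missing correct | Largest shift from 50% |
|---|---|---|---|---|---|
| 10% (plan) | 4 | 40 | 20/44 = 45.5% | 24/44 = 54.5% | 4.5 points |
| 20% (assumed) | 9 | 35 | 17.5/44 = 39.8% | 26.5/44 = 60.2% | 10.2 points |
| 30% (assumed) | 13 | 31 | 15.5/44 = 35.2% | 28.5/44 = 64.8% | 14.8 points |

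These bounds treat every loss as occurring before any guess. The plan's 10% runs to follow-up and so includes later loss, which makes the 10% row an upper limit for that setting.

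**Sampling error for comparison.** The 95% half-width of a 50% share with n = 40 is 1.96 × √(0.25/40) = 0.155, or 15.5 points.

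**Direction by arm.** Use the arm index 2p − 1, where p is the share guessing correctly. Assume that 14 of 22 sham patients and 11 of 22 real-arm patients would guess correctly, and that two patients who believe they are on sham leave each arm. In the sham arm they are correct guessers. In the real arm they are wrong guessers.

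| | All randomised | Those who stay |
|---|---|---|
| Sham arm | 14/22, index 0.27 | 12/20, index 0.20 |
| Real arm | 11/22, index 0.00 | 11/20, index 0.10 |
| Pooled share correct | 25/44 = 56.8% | 23/40 = 57.5% |

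The sham arm's blinding looks better and the real arm's looks worse, while the pooled share hardly moves. A pooled figure can therefore hide two opposite shifts.

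**The case against.** Several stronger readings are tempting, and the documents do not support them.

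- **That both times fall after everyone who quits has gone.** The end-of-treatment guess comes before any loss between the post-treatment assessment and the 3-month follow-up, so for that loss belief is on record.
- **That anyone who stops rTMS has no guess.** The section on safety monitoring and study withdrawal separates stopping rTMS from being withdrawn, and the clinical analyses follow intention to treat. A patient who stops but stays could still be asked. The end of treatment can also be read as each patient's own last session. The gap is certain only for those who leave the study during the course.
- **That the result must flatter the sham.** The remark about sham belief applies to either arm, and losing a real-arm patient with that belief removes a wrong guess. The Discussion also gives discomfort and research burden as reasons for not completing. The direction is not fixed.
- **That the link with attrition cannot be studied at all.** Withdrawal reasons are recorded and the researcher also guesses. Neither is the participant's own guess with a certainty rating, so the gap for mid-course leavers remains. The link is a Discussion point and not a listed aim. Even with complete guesses, power to test it would be low: about 19% for an assumed 22 patients per belief group and dropout of 5% against 15%. Only description is realistic.
- **That a future trial would be misled.** The progression criteria in the Feasibility section do not list blinding success.

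The article also refers to Additional file 1 for all assessments and time points, and that file was not available. It may provide for early leavers. What stands is that the article gives the timing in two places and neither reaches a patient who leaves during treatment.

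**Conclusion.** The point holds in a limited form. For patients who leave the study during the 20 sessions there is no planned guess. Blinding success is then scored without them, and their perceived allocation cannot be set against their departure.

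At the planned attrition the effect on the pooled figure is small: at most about 4.5 points, assuming that half of those who stay guess correctly and that all of about 4 losses precede any guess. This is less than the sampling error of about 15.5 points. The sampling error would show in a confidence interval, but the shift would not. It becomes material if attrition is well above plan, and the Discussion itself calls retention uncertain.

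The by-arm shifts rest on the assumption that some patients leave because they believe they are on sham. The documents raise that possibility but do not quantify it.

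**What to change.** 1. Ask for the participant's guess and its certainty at the moment of discontinuing rTMS or withdrawing, in addition to the scheduled times. Add the question to the record of withdrawals already kept. If Additional file 1 or the full protocol already provides for this, say so in the Blinding section.
2. Report blinding by arm for all randomised patients with a guess, early leavers included, and give the number without a guess in each arm.
3. Tabulate guess against completion by arm, as description only.

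The cost is one extra question and one extra table. Some leavers may decline to answer, so the gap will shrink but may not close.

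A guess at the end of week 1 could be added to the weekly questionnaires, but it is optional. It would capture belief before most departures, but it may prompt patients to think about their allocation while most sessions are still to come.
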